## Abstract

**Background:**

Clients with severe mental illness (SMI) have overall poor physical health. SMI reduces life expectancy by 5–17 years, primarily due to physical comorbidity linked to cardiometabolic risks that are mainly driven by unhealthy lifestyle behaviours. To improve physical health in clients with SMI, key elements are systematic somatic screening and lifestyle promotion. The nurse-led GILL eHealth was developed for somatic screening and the implementation of lifestyle activities in clients with SMI. Aims of this study are to evaluate the effectiveness of the GILL eHealth intervention in clients with SMI compared to usual care, and to evaluate the implementation process, and the experiences of clients and healthcare providers with GILL eHealth.

**Methods:**

The GILL study encompasses a cluster-randomised controlled trial in approximately 20 mental health care facilities in the Netherlands. The randomisation takes place at the team level, assigning clients to the eHealth intervention or the usual care group. The GILL eHealth intervention consists of two complementary modules for somatic screening and lifestyle promotion, resulting in personalised somatic treatment and lifestyle plans. Trained mental health nurses and nurse practitioners will implement the intervention within the multidisciplinary treatment context, and will guide and support the participants in promoting their physical health, including cardiometabolic risk management. Usual care includes treatment as currently delivered, with national guidelines as frame of reference. We aim to include 258 clients with SMI and a BMI of 27 or higher. Primary outcome is the metabolic syndrome severity score. Secondary outcomes are physical health measurements and participants’ reports on physical activity, perceived lifestyle behaviours, quality of life, recovery, psychosocial functioning, and health-related self-efficacy. Measurements will be completed at baseline and at 6 and 12 months. A qualitative process evaluation will be conducted alongside, to evaluate the process of implementation and the experiences of clients and healthcare professionals with GILL eHealth.

**Discussion:**

The GILL eHealth intervention is expected to be more effective than usual care in improving physical health and lifestyle behaviours among clients with SMI. It will also provide important information on implementation of GILL eHealth in mental health care. If proven effective, GILL eHealth offers a clinically useful tool to improve physical health and lifestyle behaviours.

**Trial registration:**

Clinical trial registration NCT05533749, registration date: 8 September 2022.

## Background

Clients with severe mental illness (SMI) have overall poor physical health. SMI reduces life expectancy by 5–17 years [1–3]. The high mortality rate is mostly due to natural causes such as COPD, cancer and cardiometabolic diseases [4, 5], with cardiometabolic risks (e.g. obesity, diabetes, hypertension, dyslipidaemia) as most prominent cause [1, 6]. Clients with SMI are more affected by these cardiometabolic risk factors than the general population [7]. Main reasons for the high prevalence are the adverse effects of psychotropic medications and unhealthy lifestyle behaviours such as smoking, poor diets, and physical inactivity [8–11]. Furthermore, clients receive insufficient monitoring and therapy for cardiovascular and other diseases, and use healthcare facilities and national screening programmes less often than the general population [5, 12].

To improve physical health in clients with SMI, key elements are comprehensive somatic screening and lifestyle promotion [5]. Research on the effects of somatic screening in mental health care is still scarce. More research on lifestyle promotion has been conducted, proving that lifestyle interventions can reduce weight and cardiometabolic risks in persons with SMI [13]. Lifestyle promotion also contributes to improved mental health outcomes in a selection of clients with SMI [14]. Although paying attention to lifestyle promotion is effective and considered essential care, the systematic implementation of both somatic screening and lifestyle interventions appears challenging in current mental health care [15]. To realise a better implementation of systematic screening and lifestyle promotion, multidisciplinary efforts are needed, with mental health nurses and nurse practitioners being in charge as lifestyle care managers [16, 17].

Use of eHealth can significantly contribute to effective implementation of programmes for physical health promotion in mental health care, as advised by experts [5]. eHealth can be defined as health care provided by computers or internet technology, such as websites and mobile device applications. With eHealth clients and mental health professionals can get in touch easily, and clients are enabled to gain more control over their own health and lifestyle behaviours by applying self-management strategies. Although eHealth applications for lifestyle promotion are widely available, eHealth tailored to clients with SMI is limited [18]. Thoroughly tested eHealth for clients with SMI is even scarcer. This stresses the need to probe the possibilities of eHealth for somatic screening and lifestyle interventions [5]. To investigate the potential of eHealth, this study will evaluate the nurse-led GILL (Dutch acronym for *Gezond in Lichaam en Leefstijl*, ‘Healthy in Body and Lifestyle’) eHealth intervention, developed for clients with SMI with a complementary focus on somatic screening and lifestyle promotion [19].

For this study, GILL eHealth will be implemented in different types of healthcare facilities for clients with SMI in the Netherlands. Most clients are treated by Flexible Assertive Community Treatment (FACT) teams. These teams are multidisciplinary and focus on rehabilitation, illness and symptom management, functioning in daily life, and providing recovery support [20, 21]. Clients treated by FACT teams often live independently or in assisted facilities [22]. Another relatively small portion of clients live in inpatient facilities and receive treatment and support there. These clients have significantly higher mortality rates related to physical comorbidity than clients treated by FACT teams [1]. Systematic somatic screening and lifestyle promotion is incorporated in international guidelines for all clients with SMI [23], regardless of their living situation.

As it is unknown whether clients benefit from the GILL eHealth programme in improving physical health and lifestyle behaviours, there is an urgent need to evaluate this eHealth intervention. Therefore, the first aim of this study is to evaluate the effectiveness of the GILL eHealth intervention in clients with SMI, compared to care as usual. Special focus will be on cardiometabolic health risks and diseases of clients with SMI. Second, a process evaluation will be conducted to assess the implementation and the experiences of both clients and nurses with GILL eHealth.

## Methods

### Study design

A multicentre, cluster-randomised controlled trial (RCT) with an embedded process evaluation on the execution of the GILL eHealth intervention.

### Setting

Approximately 20 mental healthcare facilities (FACT teams, assisted facilities and long-stay wards of mental hospitals) will participate in this study. The total amount of teams will depend on the recruitment rate. When the enrolment of participants is falls short, additional teams will be added. Teams will be recruited throughout different regions across the Netherlands. They will first receive brief information about the study. If they are interested in participating, an additional presentation for all team members will be provided. After this presentation the teams can decide whether they will participate in the study. An overview of participating healthcare facilities will be available at the webpage of the trial registration.

### Participants

The study population will consist of adults with SMI, according to the definition of Delespaul [24], age 18 to 65, a body mass index (BMI) of 27 or higher, and ability and willingness to participate in the intervention. All participants will sign informed consent before participating in the study. Clients are not eligible to participate if they meet any of the following criteria: contraindications due to acute psychiatric crisis or severe physical diseases (assessed by the treating physician/psychiatrist); being pregnant or breastfeeding at the time of inclusion; cognitive impairment that interferes with the ability to provide informed consent, complete study questionnaires, or participate in the intervention; lack of internet access or inability to communicate in the Dutch language.

### Randomisation

Randomisation will take place at the team level, to avoid contamination between the intervention and control groups. Before the inclusion of clients, participating teams will be randomly assigned to the GILL eHealth intervention or the control group providing care as usual. This procedure will be performed by a statistician blinded to the characteristics of the teams using a computer-generated list of numbers. To optimise comparability of the subgroups, treatment settings (FACT, assisted housing, long-stay wards) will be matched before randomisation. Blinding of clients and participating teams is not possible due to the nature of the intervention.

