### Recruitment

To recruit the eligible clients, teams will compose a list of clients who meet the inclusion and exclusion criteria. Eligible clients will be asked whether they are interested in participating in this study. After giving permission, clients will be approached by the research team and further information about the study will be provided. Participants will be asked to sign an informed consent form before the first study measurements, and are given an study number to maintain confidentiality. An overview of the study design and client flow is presented in Fig. 1. Expected date of first enrolment is estimated in November 2023.

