#### Sample size

This RCT is powered to detect a mean difference of at least 0.40 in the metabolic syndrome severity Z score across 1 year between the intervention and control group. The mean difference in the metabolic syndrome severity Z score is estimated on the basis of earlier intervention studies [27, 45]. With a power set at 0.80, and an alpha of 0.05, two groups of 98 patients with SMI are needed in each group. Assuming an inclusion of 10 clusters (teams) within each arm, and assuming an ICC of 0.01 implies that 220 patients are required. Assuming a dropout rate of 15% [46, 47] and testing the intervention effect using two samples t-test, implies that we need to recruit a total of 258 patients. However, testing of the intervention effect by use of linear mixed models is likely to reduce bias and increase power [48].

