## Discussion

Limited eHealth-supported lifestyle interventions are available for clients with SMI, tailored to their specific needs and characteristics. However, given the overall burden of poor physical health on clients with SMI [7], there is an urgent need for systematic somatic screening and effective lifestyle interventions. This paper presents the design of the GILL eHealth intervention. This cluster RCT will provide new information on the effects of systematic somatic screening and lifestyle promotion on physical health in clients with SMI. It also gives new insights on the use of eHealth in this population. The process evaluation will lead to the development of an implementation guide. This might provide additional information on the implementation of eHealth programmes, which could be used for broad implementation of GILL eHealth and future eHealth modules.

A strength of this study is its pragmatic design. The study will be conducted in mental health teams and implemented as part of essential care. In this way clients, treatments, and procedures resemble daily clinical practice. This increases the generalisability of the study outcomes. Another way the generalisability is enhanced is by including clients with SMI who receive care within different treatment settings. This limits the treatment setting as influencing factor on effectiveness and implementation. An additional strength is the quality of the GILL eHealth intervention. GILL eHealth is the result of a long-term development trajectory and is adapted to the preferences of clients and nurses. The intervention is based on current national and international guidelines [19]. It is therefore a realistic assumption that the GILL eHealth intervention will be more effective than usual care in improving physical health and lifestyle behaviours.

The GILL eHealth intervention does not allow for blinding of participants and nurses for the study. However, this reflects the daily practice and matches the pragmatic study design. Most important is to prevent contamination between the two study conditions – therefore the cluster-randomised design will be applied, in which the nurses working in the usual care teams will not receive training.

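### FACT teams and assisted-housing facilities are randomised separately although they may share clients, so the two teams serving one client can be allocated to opposite arms

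*Protocol article*

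**What the plan says.** The Setting section names the participating units: "Approximately 20 mental healthcare facilities (FACT teams, assisted facilities and long-stay wards of mental hospitals) will participate in this study". It adds that teams come from different regions and that more will be added if enrolment falls short.

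The Randomisation section gives the purpose of the cluster design: "Randomisation will take place at the team level, to avoid contamination between the intervention and control groups". To make the arms comparable, "treatment settings (FACT, assisted housing, long-stay wards) will be matched before randomisation". Allocation precedes client inclusion and is done by a statistician blinded to team characteristics.

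The Background section, describing the settings in which GILL will be implemented, says: "Clients treated by FACT teams often live independently or in assisted facilities".

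Under Recruitment, "teams will compose a list of clients who meet the inclusion and exclusion criteria".

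The Discussion section ranks the aim of separation highly ("Most important is to prevent contamination between the two study conditions") and gives the mechanism: "therefore the cluster-randomised design will be applied, in which the nurses working in the usual care teams will not receive training".

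The Usual care section adds a second safeguard. Control clients keep unrestricted access to mental and general health care but may not take part in a structured lifestyle programme during the study.

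**The concern.** Randomising teams prevents contamination only if each client is served by one randomised unit. By the article's own description, FACT treatment and assisted housing are not mutually exclusive: one is a treating team, the other a place where its clients often live. Matching FACT with FACT and housing with housing balances the settings, but it does not tie a FACT team to a facility that houses its clients.

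A client of a usual-care FACT team could therefore live in a facility allocated to GILL. Under Training of care managers, two nurses per intervention team are trained and can pass their knowledge to colleagues. A control client exposed in this way moves the control arm toward the intervention arm and biases the estimated difference toward zero. In the reverse case, a GILL FACT client living in a usual-care facility, there is little dilution, but it is unclear which cluster the client should count in.

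If such overlap were common, a null result would be hard to tell apart from contamination, which is what the design is meant to exclude.

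**Working it through.** **Whether the situation can arise**

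1. FACT teams and assisted facilities are both units of randomisation (Setting, Randomisation).
2. FACT clients often live in assisted facilities (Background). No proportion is given, and the same sentence also names independent living.
3. No step described allocates units that share clients together. The statistician is blinded to team characteristics, so a link would have to be identified before allocation.
4. If a linked FACT team and facility are allocated independently 1:1 within their own setting (an assumption), they fall in opposite arms with probability 0.5.

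**What the safeguards cover**

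- Leaving usual-care teams untrained stops spread through those teams' own nurses. It does not affect a trained nurse in the facility where a control client lives.
- The bar on structured lifestyle programmes plausibly excludes formal use of MyGILL, the lifestyle module. It does not clearly exclude OurGILL, the somatic screening module, particularly as control clients keep unrestricted access to care. It does not address informal coaching.

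**The plan's own figures**

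The trial is "powered to detect a mean difference of at least 0.40 in the metabolic syndrome severity Z score across 1 year", with power 0.80, alpha 0.05 two-sided, 98 per group, 10 clusters per arm, ICC 0.01 and 15% dropout. The SD is not stated; SD 1 is assumed.

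- Per group: n = 2 × (1.96 + 0.84)² × 1² / 0.40² = 98 (stated 98; 99 with a t-test).
- Clustering: with 11 clients per cluster the design effect is 1 + (11 − 1) × 0.01 = 1.10. Then 2 × 98 × 1.10 = 215.6, and 2 × 100 × 1.10 = 220 (stated 220).
- Dropout: 220 / 0.85 = 258.8 (stated 258).

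The sample size reproduces within rounding. The issue is the design, not the arithmetic.

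**Illustration of dilution**

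Assume a share q of control clients receives the full effect of GILL through a second team. The expected difference is 0.40 × (1 − q). With SE = √(2/98) = 0.143 and power = Φ(0.40(1 − q)/0.143 − 1.96):

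| q | Expected difference | Power, 98 per arm | Power, about 219 analysed, ICC 0.01 |
|---|---|---|---|
| 0 | 0.40 | 0.80 | 0.81 |
| 10% | 0.36 | 0.71 | 0.72 |
| 20% | 0.32 | 0.61 | 0.62 |

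The last column uses 258 × 0.85 = 219 analysed clients and a design effect of 1.10.

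**How demanding these values of q are**

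If linked units differ in arm half the time, q = 10% needs about 0.10 / 0.5 = 20% of control clients to be served by two participating units, and q = 20% needs about 40%. All of those in opposite arms would also have to receive the full effect. If exposed controls received half the effect, a 20% share would give the 10% row. The document supports no particular value of q.

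**The case against.** The case against has several parts.

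- **The usual-care rule.** Control clients are barred from structured lifestyle programmes, and GILL contains one. This stands in part: it makes full exposure unlikely, but leaves screening and informal coaching open.
- **The Background sentence is about residence.** It does not say that those residences take part in the trial, or that their staff would deliver GILL to FACT clients. Dilution needs a participating FACT team, a participating facility, opposite allocation and actual exposure. With about 20 teams across regions, this may be uncommon. This stands, and it is why no size can be claimed.
- **GILL is not ambient.** It is an eHealth product whose two modules take at least two hours to implement with a coordinating nurse. Living near trained staff is not receiving the intervention. This also stands against reading the power figures as a forecast.
- **An article omits operational detail.** A rule for clients known to two teams may be in the full protocol. That answers a complaint about a missing definition. It does not answer the point that the stated units and matching leave overlapping units free to fall in opposite arms.

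A reader might go further and infer that mixed exposure does occur in both directions, that shared clients have no defined arm, that teams would steer such clients to a preferred arm, or that adding teams increases local overlap. The document supports none of these. It reports no shared client. The natural reading of Recruitment is that a client takes the arm of the team through which he or she is enrolled. Nothing is said about teams' preferences, and added teams are not said to be local.

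**Conclusion.** The point holds as a gap in the randomisation scheme. FACT teams and assisted facilities are allocated separately within setting, the article says their clienteles can overlap, and neither the matching nor the two stated safeguards fully protects a client whose two teams land in opposite arms. The likely direction of bias is toward no effect.

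The size is unknown. Power of 0.71 at q = 10% and 0.61 at q = 20%, against the planned 0.80, assumes SD 1, 98 per arm and full exposure of the share q, none of which the article establishes. The figures show only that the plan has almost no margin above 0.80. The true loss may be close to nil if few or no participating units share clients. The change is still worth making, because the check costs little before allocation and exposure cannot be undone afterwards.

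**What to change.** Add to the randomisation procedure:

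1. Before randomisation, ask each team which other participating units serve its clients.
2. Randomise units that share clients as one allocation unit.
3. Define each client's cluster as the team providing the coordinating nurse.
4. Do not enrol clients who are served by participating teams in opposite arms.
5. Apply the same check to teams added later. Randomise them if they share no clients with an allocated team. Otherwise do not add them, or do not enrol the shared clients. A late team should not simply be placed in the linked team's arm, because that allocation would be non-random and known in advance.

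The cost is one question per team and a few sentences of text. A combined FACT and housing unit fits none of the three matched settings, so linked units need their own matching category. A few clients may not be enrolled.

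Joining units may also leave slightly fewer than the 10 clusters per arm assumed. With 9 per arm and 219 analysed, the average cluster is 219 / 18 = 12.2 clients and the design effect is 1 + 11.2 × 0.01 = 1.11 instead of 1.10, before any allowance for unequal cluster sizes.

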### Recruitment

To recruit the eligible clients, teams will compose a list of clients who meet the inclusion and exclusion criteria. Eligible clients will be asked whether they are interested in participating in this study. After giving permission, clients will be approached by the research team and further information about the study will be provided. Participants will be asked to sign an informed consent form before the first study measurements, and are given an study number to maintain confidentiality. An overview of the study design and client flow is presented in Fig. 1. Expected date of first enrolment is estimated in November 2023.

**Fig. 1 Fig1:**
[figure not shown]
Overview of the study design and participant flow

### GILL eHealth intervention

The GILL eHealth intervention was developed by two nurse practitioners and a professor of mental health nursing. The content is developed in accordance with the 2015 national guidelines on somatic screening and lifestyle intervention for clients with SMI [19]. The total refinement of GILL eHealth took approximately 10 years, developing and testing different predecessors. One predecessor, the Traffic Light Method for lifestyle promotion, showed an improvement of physical health outcomes in a pilot study [25]. GILL eHealth will be available on the platform of eHealth provider Minddistrict, ensuring appropriate technical support for the eHealth users. The intervention is both android- and iOS-compatible. GILL eHealth is a practice- and evidence-based tool that integrates somatic screening and lifestyle promotion, resulting in a personalised treatment and lifestyle plan. The intervention consists of two modules, OurGILL (somatic screening) and MyGILL (lifestyle promotion).

